### Invasive testing

Patients will undergo cardiac catheterisation via the femoral artery and either the femoral or internal jugular vein following appropriate consent. A 7F sheath will be placed in the vein and artery. A Cordis-Webster (Cordis Webster, Inc., Baldwin Park, CA, USA) 7F coronary sinus (CS) thermodilution catheter will be guided into the coronary sinus and 50/50 saline/contrast injections will allow visualisation and confirmation of its position within the right atrium and CS. All catheters will be calibrated prior to utilisation. The catheter is connected to both a Medtronic (Medtronic Inc., [name], MN, USA) temporary pacemaker 5348 and to a specialised Wheatstone bridge coupled to a bank of isolated direct coupled bioamplifiers (Coulbourn Instruments, Whitehall, PA). The output is subsequently digitised using a Dataq DI720 data acquisition system and both displayed and stored on a laptop computer using Windaq software (Dataq, Akron, OH). The atria will then be paced via electrodes on the catheter in the coronary sinus.

A 7F dual-field conductance catheter (CA-71103-PL catheter, CD Leycom, The Netherlands) will then guided via the femoral artery sheath through the aortic valve and positioned within the left ventricle. Blood samples will then be taken from the left ventricle and CS for cross heart substrate analysis prior to the administration of heparin. The atria will then be paced at a rate just above baseline to ensure a steady rate. The conductance catheter allows continuous and simultaneous sampling of pressure and volume at 4 ms intervals, allowing the acquisition of pressure-volume loops in real-time. CS thermodilution runs will be performed in triplicate (with an average of 3 runs used for analysis). Samples will then be taken for oxygen and carbon dioxide measurement. Oxygen measurement will be performed using a Bayer Rapidlab 800 series blood gas analyser (Bayer Healthcare LLC, East Walpole, MA, USA). Carbon dioxide measurement will be performed by mass spectrometry by the University of Brimingham using a Finnigan MAT Delta^plus^X mass spectrometer. PV loops will be acquired from the left ventricle with a CFL-512 system (CD Leycom), which allows further offline analysis (CircLab, Leiden University, The Netherlands) for determination of left ventricular stroke work (LVSW), mechanical efficiency, dp/dt_max_, dp/dt_min_, and Tau (rate of active relaxation).

The steady heart rate will allow for accurate assessment of per beat myocardial oxygen consumption. All of this subgroup will have had CMR studies for accurate assessment of cardiac mass and thus permit correction for myocardial mass.

Respiratory quotient (RQ) is a unitless value found by dividing the amount of eliminated CO_2 _by the O_2 _consumed [1].(1)

Mechanical efficiency (ME) can be calculated by dividing work output by work input giving another dimensionless value or percentage [2].(2)

Work input can be calculated from myocardial oxygen consumption measurements according to the Fick principle by multiplying coronary sinus blood flow by the ateriovenous oxygen content difference[18]. To be used in the above equation the caloric equivalent of 1 mL of O_2 _is ≈20J will be used[19].

External work will be estimated from measurements taken from the PV loops acquired from the left ventricle. 1 mmHg × mL equates to 1.33 × 10^-4 ^J for the purposes of calculating ME[19].

### Randomisation and Drug Monitoring

Following baseline investigations ensuring normal liver function tests, participants will be randomised by computer to commence with perhexiline 200 mg oral daily or an identical placebo for one month (Figure 1). Randomisation will be done in a 50:50 ratio of perhexiline:placebo in blocks of 10.

At one week duration, all patients will have a blood sample taken for serum perhexiline level with the researcher blinded to the subject's treatment allocation. This level will be evaluated by a doctor unblinded to the subject's treatment allocation. The dosage of perhexiline will be adjusted according to the accepted dosing protocol (Table 2). An equal number of dummy dose adjustments will be made to those patients on placebo to help to maintain blinding.

**Table 2 T2:** Perhexiline dose titration according to serum perhexiline level.

*Perhexiline concentration (mg/L)*	*Recommended new daily dose (mg)*
0.00-0.05	300
0.05-0.15	250
0.15-1.00	200
1.00-1.50	100
1.50-2.00	50
>2.00	Cease for 1 week and start 50 mg alternate days

At the end of one month of therapy, patients will undergo a repeat of baseline investigations and a further perhexiline level will be taken to ensure therapeutic levels were achieved and compliance maintained.

### Endpoints

The primary end point of the study will be an increase in the PCr/ATP ratio as assessed by MRS after 4 weeks of treatment. This end point has been used in previous studies and is associated with symptomatic class and mortality in heart failure[20]. Secondary endpoints are: i) respiratory quotient; ii) mechanical efficiency; iii) change in LV function.

### Planned Statistical Analysis

Comparisons will be performed between the groups at baseline and after the 4 week treatment. The normality of distribution of all continuous variables will be determined using a normality plot and the Kolmogorov-Smirnov test. Normally distributed variables will be analysed using unpaired t-tests, χ^2 ^or repeated measures analysis or variance. Variables not normally distributed will be log transformed prior to analysis to achieve normal distribution or, if this is not achieved, analysed by Mann-Whitney U or Kruskal-Wallis tests.

Analysis will be by intention-to-treat. A *p*-value of < 0.05 will be considered statistically significant.

Sample size calculations were based on the primary end point of change in PCr/ATP ratio after 4 weeks of treatment. Pilot work from our group using the same MRS technique and perhexiline revealed a 0.4 improvement in PCr/ATP ratio in the treatment group by comparing means. The response was normally distributed with a standard deviation of 0.5. Using this data, 26 subjects in each arm will provide at least 80% power of detecting a 0.4 change in PCr/ATP ratio using a two-tailed t-test at the 5% significance level. Recruiting 50 patients will allow for withdrawal, drop out or incomplete data.

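### The primary analysis of PCr/ATP is not tied to the change on which the trial is sized, and none of the listed tests uses the measured baseline as a covariate; ANCOVA would be more efficient at almost no cost

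*Protocol article*

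**What the plan says.** The Endpoints section defines the outcome as a rise: "The primary end point of the study will be an increase in the PCr/ATP ratio as assessed by MRS after 4 weeks of treatment". The sizing paragraph of Planned Statistical Analysis treats it as a change: "Sample size calculations were based on the primary end point of change in PCr/ATP ratio after 4 weeks of treatment". Its inputs are pilot work that "revealed a 0.4 improvement in PCr/ATP ratio in the treatment group by comparing means", and a spread given as "The response was normally distributed with a standard deviation of 0.5". The result is that "26 subjects in each arm will provide at least 80% power of detecting a 0.4 change in PCr/ATP ratio". The test behind that figure is a two-sided t-test at 5%.

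The analysis paragraph of the same section begins: "Comparisons will be performed between the groups at baseline and after the 4 week treatment". It continues: "Normally distributed variables will be analysed using unpaired t-tests", with chi-squared and repeated measures analysis of variance as the other options. This list covers all normally distributed variables. It does not say which test applies to PCr/ATP, or whether the variable tested is the 4-week value or the change.

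Under Baseline Studies, spectroscopy for PCr/ATP is part of the baseline visit for all patients, and the baseline tests are repeated in full after one month. Both values are therefore planned for every patient.

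**The concern.** The sizing and the analysis text do not point clearly to the same quantity. The sizing uses change. The opening analysis sentence reads most directly as one comparison of the arms at each visit. A t-test on 4-week values and a t-test on change have different standard deviations, so the same 50 patients give different power, and the article leaves the choice open.

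None of the named tests is a regression of the 4-week value on arm and baseline. In a trial of about 25 per arm, a chance difference between the arms in baseline PCr/ATP carries over into an unadjusted 4-week comparison as extra variance. A change score removes that difference but over-corrects when the correlation is below 1. ANCOVA uses the correlation that the data show.

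The first of the two planned comparisons, between arms at baseline, tests a difference that randomisation has already made a matter of chance. It answers no question about treatment.

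**Working it through.** **Inputs.** Difference 0.4, SD 0.5 and two-sided 5% come from Planned Statistical Analysis. The 50 patients randomised 1:1, so 25 per arm, come from Study Design and Randomisation and Drug Monitoring. The correlation *r* between baseline and 4-week PCr/ATP is not given and is taken as 0.3 to 0.8 by assumption. SDs are assumed equal at both visits and in both arms.

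**1. The plan's own figure.** For a two-sample t-test the noncentrality is 0.4 / (SD × √(2/n)), with 2n − 2 degrees of freedom.
- 26 per arm: 0.4 / (0.5 × √(2/26)) = 2.884, power 80.7%. The stated 26 per arm reproduces.
- 25 per arm: 0.4 / (0.5 × √(2/25)) = 2.828, power 79.1%.

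**2. Taking 0.5 as the SD of change** (the more natural reading of a response).
- Change score: SD 0.5 at any *r*. With two visits, the group-by-time test of a repeated measures ANOVA is the same test.
- 4-week value: SD = 0.5 / √(2(1 − r)).
- ANCOVA: residual SD = SD of the 4-week value × √(1 − r²) = 0.5 × √((1 + r)/2).

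Power at 25 per arm:

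| r | SD, 4-week value | 4-week t-test | Change score | SD, ANCOVA | ANCOVA |
|---|---|---|---|---|---|
| 0.3 | 0.423 | 91% | 79% | 0.403 | 93% |
| 0.5 | 0.500 | 79% | 79% | 0.433 | 89% |
| 0.7 | 0.645 | 57% | 79% | 0.461 | 85% |
| 0.8 | 0.791 | 42% | 79% | 0.474 | 83% |

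Charging ANCOVA one degree of freedom (47 instead of 48) leaves the rounded figures unchanged.

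**3. Where the order changes.** The 4-week SD exceeds the change SD when 2(1 − r) < 1, that is, when r > 0.5. Below 0.5 the 4-week t-test has more power than the change score. ANCOVA beats the change score at every r below 1, because √((1 + r)/2) < 1. It beats the 4-week t-test at every r above 0, because √(1 − r²) < 1.

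**4. Taking 0.5 as the SD of the 4-week value instead.** The SD of change is then 0.5 × √(2(1 − r)) and the ANCOVA SD is 0.5 × √(1 − r²). Power at 25 per arm:

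| r | 4-week t-test | Change score | ANCOVA |
|---|---|---|---|
| 0.3 | 79% | 65% | 83% |
| 0.5 | 79% | 79% | 89% |
| 0.7 | 79% | 95% | 97% |
| 0.8 | 79% | 99.2% | 99.6% |

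Under either reading of the SD, ANCOVA has the highest power at every correlation examined.

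**The case against.** The strongest reply is that the plan does not commit to an unadjusted 4-week t-test. The endpoint is worded as an increase, the sizing calls it a change, and an unpaired t-test can be run on change scores. On that reading sizing and analysis agree. This stands: the defect is that the analysis is left open, not that a mismatched one has been fixed.

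Three stronger readings are tempting, and the article supports none of them.
- A reader might infer that the plan ignores the baseline altogether. It lists repeated measures ANOVA, whose group-by-time test uses each patient's baseline and matches the sizing. What is absent is a model with baseline as a covariate.
- A reader might take the group main effect of that ANOVA, which averages in the pre-treatment visit, to be the planned treatment test. Nothing in the article says so.
- A reader might conclude that power is lost against the sizing. That needs a 4-week t-test, 0.5 as the SD of change and r above 0.5. The article fixes none of the three.

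It is also fair to say that validity is not at stake. Under randomisation the 4-week, change-score and group-by-time tests are all unbiased with the right type I error, and chance imbalance is already reflected in the standard error. Testing baseline is uninformative, but no decision is said to depend on it.

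Finally, this is a condensed article, and a full protocol or analysis plan may name the model. The point therefore rests on what the article does state: it chooses tests, and a better one is available from data it already collects.

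**Conclusion.** The point holds as a matter of efficiency and of fixing the primary analysis, not as an error that invalidates the trial. The article sizes on change, describes comparisons at each visit, and ties none of its listed tests to the primary endpoint.

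With 0.5 as the SD of change and 25 per arm, ANCOVA gains about 14, 10, 6 and 4 percentage points over a change-score test at r = 0.3, 0.5, 0.7 and 0.8. Over a 4-week t-test it gains about 2, 10, 28 and 41 points. With 0.5 as the SD of the 4-week value, ANCOVA has about 83% to over 99% power over the same range, against 79% for the 4-week t-test.

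The gain is useful because there is little slack: the sizing asks for 26 per arm, and 25 per arm gives 79.1% on the plan's own test. The sizes rest on an assumed correlation and on equal SDs at both visits. That ANCOVA ranks first does not depend on which meaning the 0.5 has.

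**What to change.** In Planned Statistical Analysis, name one primary analysis: ANCOVA of 4-week PCr/ATP on treatment arm with baseline PCr/ATP as covariate, reporting the adjusted mean difference with its 95% confidence interval and two-sided p-value. Use the same model for LVEF and other continuous measures taken at both visits. Describe baseline values by arm without significance tests. State whether the 0.5 in the sizing is the SD of change or of the 4-week value.

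This changes wording only. It costs one degree of freedom for the covariate and needs no extra patients, visits or measurements.

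### A normality check on the trial data chooses the primary test, so the primary estimand is not fixed in advance; and the prescribed log step cannot be applied if change in PCr/ATP is analysed

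*Protocol article*

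**What the plan says.** The Planned Statistical Analysis section sets a three-step rule for every continuous variable.

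- **Check:** "The normality of distribution of all continuous variables will be determined using a normality plot and the Kolmogorov-Smirnov test".
- **If normal:** unpaired t-tests or repeated measures ANOVA (χ² is listed alongside).
- **If not normal:** "Variables not normally distributed will be log transformed prior to analysis to achieve normal distribution or, if this is not achieved", the variable goes to Mann-Whitney U or Kruskal-Wallis.

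The primary endpoint is not exempted. Nothing is said about values that are zero or negative.

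The same section says "Sample size calculations were based on the primary end point of change in PCr/ATP ratio after 4 weeks of treatment", and powers the trial "using a two-tailed t-test at the 5% significance level". The Endpoints section calls the primary endpoint an increase in PCr/ATP and lists change in LV function as a secondary endpoint. The sentence that opens the statistical section speaks only of comparing the groups at baseline and after treatment. It does not say whether the compared quantity is the week-4 level or the change. Analysis is by intention to treat.

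**The concern.** The three branches answer different questions. A t-test on the natural scale estimates a difference in means. A t-test on logs estimates a ratio of geometric means. A rank test compares orderings. Under the stated rule, which of these becomes the primary result is known only after the outcome data have been examined, partly through a plot that has to be interpreted by eye. The section does not say whether the Kolmogorov-Smirnov test is corrected for estimated parameters, whether it is run per arm or pooled, or what happens if plot and test disagree. Only one branch corresponds to the sample-size calculation.

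There is also a technical fault. A change score can be zero or negative, and the logarithm is then undefined. If the change is what is analysed, the middle step of the rule cannot be carried out on the primary endpoint or on change in LV function.

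**Working it through.** **Inputs.** From Planned Statistical Analysis: improvement 0.4 ("revealed a 0.4 improvement in PCr/ATP ratio in the treatment group by comparing means"), SD 0.5 ("The response was normally distributed with a standard deviation of 0.5"), two-sided 5% t-test, and "26 subjects in each arm will provide at least 80% power of detecting a 0.4 change in PCr/ATP ratio". From Randomisation and Drug Monitoring: 1:1 allocation, so 50 recruited means 25 per arm. Assumed, because the article does not give them: placebo mean change 0, with the same SD of 0.5.

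**1. The plan's own figure.** Standardised difference = 0.4/0.5 = 0.8. The exact two-sample t-test calculation gives 25.52 per arm, rounded up to 26, with power 80.75% at 26. The stated 26 reproduces, but only for a t-test on the untransformed scale.

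**2. Can a change be logged?** P(change ≤ 0) = Φ(−mean/SD).

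- Perhexiline: Φ(−0.4/0.5) = Φ(−0.8) = 0.212; 25 × 0.212 = 5.3 subjects.
- Placebo: Φ(0) = 0.5; 25 × 0.5 = 12.5 subjects.
- Total: 5.3 + 12.5 = 17.8, about 18 of 50.
- Probability that all 50 changes are positive: (1 − 0.212)^25 × 0.5^25 ≈ 8 × 10⁻¹¹.

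For change in ejection fraction, the figures in Study Limitations (mean improvement 10, SD about 10) give Φ(−10/10) = Φ(−1) ≈ 16% of treated changes at or below zero.

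**3. Which test would the rule choose?** The rule was simulated with 25 per arm, 3,000 trials per scenario and the normality check run per arm. It used the t-test if both arms passed, then the log if all values were positive and the logs passed, otherwise Mann-Whitney. The change distributions have SD 0.5. The week-4 level is an assumed lognormal with median 1.6 and log-SD 0.3. The table gives the percentage of trials sent to t-test / log / Mann-Whitney when there is no treatment difference.

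| Data | KS with Lilliefors correction | Uncorrected KS |
|---|---|---|
| Change, normal | 91 / 0 / 9 | 100 / 0 / 0 |
| Change, t with 3 df | 50 / 0 / 50 | 91 / 0 / 9 |
| Change, shifted exponential | 9 / 0 / 91 | 85 / 0 / 15 |
| Week-4 level, lognormal | 66 / 27 / 7 | 99.5 / 0.5 / 0 |

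The log branch was never reached for a change. For a positive level it was reached, so there all three estimands are possible. The choice also depends heavily on which version of the test is run.

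**4. Error rates.** Type I error of the whole rule was 4.5% to 5.5% across these scenarios. With a true difference of 0.4 and the corrected test, power of the rule against an always-used t-test was 79.3% v 79.6% (normal), 93.3% v 84.3% (t, 3 df) and 93.9% v 79.9% (exponential). Mann-Whitney alone on normal changes gave 76.8%.

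**5. Precision of a fixed alternative.** With equal variance σ² at both visits and correlation ρ, the per-subject variances are σ² for week-4 values, 2σ²(1 − ρ) for change and σ²(1 − ρ²) for ANCOVA. At an assumed ρ = 0.5 these are σ², σ² and 0.75σ², so ANCOVA has a variance ratio of 0.75 against either.

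**The case against.** The strongest reply is that the rule does little damage in operation. It ends in a rank test, so a variable whose log cannot be taken still gets an analysis that uses every subject. Simulated type I error stays near 5%, and power is about the same as, or better than, that of an always-used t-test. The pilot response is reported as normal and the trial is powered on a t-test, so the expected primary test can be identified. An uncorrected Kolmogorov-Smirnov test has little power at this size and would usually leave the t-test in place. All of this stands, and it limits the point.

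It can also be said that the log problem depends on reading the endpoint as a change. If week-4 PCr/ATP levels are compared, which the opening sentence of the section permits, the values are positive and the log is defined. That also stands, but the sample-size text says change, and under the level reading the estimand is still chosen by the data.

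A reader might infer something stronger: that subjects who did not improve would be dropped when the change is logged, with a collapse in power. The documents do not support that. Nowhere does the article tell the analyst to delete non-positive values, it specifies intention to treat, and the rank-test fallback retains everyone.

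Finally, a condensed article may leave the detailed model to a fuller plan. Here, though, the article states a rule and applies it to all continuous variables, so this is not an omission.

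**Conclusion.** The point holds in a limited form. The article's rule leaves the primary test, and what it estimates, to be determined by the outcome data, and only one of its branches matches the stated sample size. If change in PCr/ATP is analysed, the log step is unusable: about 18 of 50 changes would be at or below zero. That count rests on the article's 0.4 and 0.5 plus an assumed placebo mean of 0 with the same SD. If week-4 levels are analysed, the log works, but the estimand remains open.

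The consequence is loss of pre-specification and of a clear interpretation of the primary result. No dropped subjects, material loss of power or inflation of type I error has been shown. The diversion rates in the table depend on the assumed distributions and on the version of the normality test. The point is worth correcting because the correction is nearly free.

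**What to change.** Name one primary analysis: ANCOVA of untransformed 4-week PCr/ATP with baseline PCr/ATP as covariate, reported as an adjusted mean difference with its confidence interval, whatever a normality test shows. Add one named sensitivity analysis, either rank-based or a permutation p-value. Do the same for LV function, modelling the 4-week value on its baseline. Where a log scale is wanted for a skewed variable, apply it to the raw positive values and never to a change. Remove the Kolmogorov-Smirnov test as the means of choosing between tests; normality plots can stay as description.

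An unpaired t-test on the change would also fix the test and would match the sample-size calculation. ANCOVA is preferred because baseline PCr/ATP is already measured in every patient and the adjustment gains precision (variance ratio about 0.75 at an assumed correlation of 0.5).

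The cost is a change of wording and slightly more analysis work. No new data and no change in sample size are needed for this point.

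### The trial is sized on change in PCr/ATP from pilot figures not shown to be net of control, the primary comparison is not tied to that calculation, and the 50 recruited give 79% power, not at least 80%

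*Protocol article*

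**What the plan says.** All of this is in the Protocol article, mostly under Planned Statistical Analysis.

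- **Variable used for sizing:** the change in PCr/ATP over 4 weeks.
- **Effect:** the pilot "revealed a 0.4 improvement in PCr/ATP ratio in the treatment group by comparing means". No pilot control figure is given.
- **SD:** "The response was normally distributed with a standard deviation of 0.5".
- **Claim:** "26 subjects in each arm will provide at least 80% power" to detect a change of 0.4, "using a two-tailed t-test at the 5% significance level".
- **Recruitment:** 50 patients, which the article says allows for withdrawals and incomplete data. Under Randomisation and Drug Monitoring: "Randomisation will be done in a 50:50 ratio of perhexiline:placebo in blocks of 10". That means 25 per arm.
- **Analysis:** "Comparisons will be performed between the groups at baseline and after the 4 week treatment". For normally distributed variables the article lists unpaired t-tests, chi-square or repeated measures ANOVA. It assigns none of them to the primary endpoint.

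Study Limitations then says, without qualification, that the study is powered for the primary endpoint.

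**The concern.** The trial compares perhexiline with placebo, so the effect that determines power is the difference between arms. The natural reading of the pilot sentence is an improvement in treated patients and the SD of that improvement. If so, the calculation carries an unstated assumption that placebo patients do not improve over 4 weeks.

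The planned comparison is also loosely tied to the calculation. An SD of change fits a test of change. The analysis text can be read as an unpaired t-test on the 4-week values, for which a different SD applies.

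Finally, the power claim is attached to 26 per arm, while the trial recruits 25 per arm. What is at stake is how a null primary result will be read: the article presents the trial as adequately powered, and a reader could take a null result as stronger evidence against an effect than the design supports.

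**Working it through.** **Inputs from the article:** difference 0.4, SD 0.5, two-sided 5% t-test, 1:1 allocation, 26 per arm stated, 25 per arm recruited. **Assumed, because the article gives neither:** the placebo change, and the correlation r between baseline and 4-week PCr/ATP.

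**Method.** Exact power from the noncentral t distribution with 2n − 2 degrees of freedom and noncentrality δ / (SD × √(2/n)).

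**1. The stated figure.** At n = 26, the noncentrality is 0.4 / (0.5 × √(2/26)) = 2.88 and power is 80.7%; 26 is the smallest n per arm that reaches 80%. A one-sample test of the same 0.4 and 0.5 would need only 15 patients. So 0.4 entered as the between-arm difference and 0.5 as the common SD.

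**2. The number recruited.** At n = 25, the noncentrality is 0.4 / (0.5 × √(2/25)) = 2.83 and power is 79.1%. With 24 evaluable per arm it is 77.4%, and with 22 it is 73.6%.

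**3. If 0.4 is a treated-group change.** The between-arm difference is 0.4 minus the placebo change. With SD 0.5:

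| Placebo change (assumed) | Net difference | Power, 25 per arm | n per arm for 80% |
|---|---|---|---|
| −0.10 | 0.50 | 93% | 17 |
| −0.05 | 0.45 | 88% | 21 |
| 0 | 0.40 | 79% | 26 |
| +0.05 | 0.35 | 68% | 34 |
| +0.10 | 0.30 | 55% | 45 |
| +0.20 | 0.20 | 28% | 100 |

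**4. If 0.5 is the SD of change.** With equal variances at the two visits, SD of change² = 2(1 − r) × SD of 4-week values². Hence:

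- SD of 4-week values = 0.5 / √(2(1 − r));
- SD after adjustment for baseline = SD of 4-week values × √(1 − r²) = 0.5 × √((1 + r)/2).

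For a difference of 0.4 at 25 per arm:

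| r (assumed) | SD, 4-week values | Power, 4-week values | SD, baseline-adjusted | Power, baseline-adjusted |
|---|---|---|---|---|
| 0.3 | 0.423 | 91% | 0.403 | 93% |
| 0.5 | 0.500 | 79% | 0.433 | 89% |
| 0.6 | 0.559 | 70% | 0.447 | 87% |
| 0.7 | 0.645 | 57% | 0.461 | 85% |
| 0.8 | 0.791 | 42% | 0.474 | 83% |

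A test of change scores has 79% at every r. Raw 4-week values fall below 80% once r reaches about 0.5. The baseline-adjusted comparison is never worse than either.

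**5. If 0.5 is instead the SD of the 4-week values.** The adjusted SD is 0.5 × √(1 − r²), which cannot exceed 0.5. Adjustment therefore does not lower power on this reading either, apart from the loss of one degree of freedom.

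**The case against.** The strongest reply is that nothing was miscalculated: 26 per arm is correct for the inputs given, and only their meaning is in doubt. That stands. Four further points also carry weight.

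- **The pilot figure may already be a between-group one.** The reference to comparing means, and to a treatment group at all, could imply a pilot control. The article does not settle this.
- **Little placebo drift may be expected.** Patients are stable on therapy, are selected on ejection fraction rather than on PCr/ATP, and have spectra read by a single blinded operator with a fixed voxel size. Assuming no placebo change is a conventional planning choice.
- **Change may in fact be what is tested.** With two visits and two arms, the group-by-time test in the listed repeated measures ANOVA is equivalent to an unpaired t-test on change, and the sizing text names change as the variable.
- **Choosing among listed tests may belong to a fuller document.** That is fair for a condensed article, so the missing detail alone would not be a finding.

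A reader might infer that the stated power holds only if placebo does not change and only if change scores are tested. The documents do not support that. A placebo decline raises power, 4-week values keep about 80% or more when r is about 0.5 or lower, and baseline adjustment does better than change scores.

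The reply does not answer two things. The article's own recruitment target falls short of its own power statement. And the analysis text leaves open a comparison that could cost substantial power, although the baseline scan that would prevent this is already being collected.

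**Conclusion.** The point holds in a limited form.

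**Firm, from the article's own figures:** the 50 recruited give 79% power for a 0.4 difference with SD 0.5 before any dropout, against a claim of "at least 80% power of detecting a 0.4 change in PCr/ATP ratio". The shortfall at full recruitment is about one percentage point, and it grows with any loss of patients.

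**Conditional:** power is sensitive to what the pilot figures mean and to which comparison is primary. It is 55% at 25 per arm if 0.4 is a treated-group change and placebo improves by 0.10. It is 57% if raw 4-week values are compared, 0.5 is the SD of change and r = 0.7. The placebo change and r are assumptions that show sensitivity; they are not estimates for this trial.

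**Not shown:** that the pilot effect was wrongly taken from a single arm, or that the SD belongs to a different analysis from the one intended. The wording permits both readings and establishes neither.

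**What to change.** Three edits under Planned Statistical Analysis:

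1. Name the primary comparison as the 4-week PCr/ATP ratio between arms, adjusted for the baseline ratio (ANCOVA), in place of an unpaired t-test on the 4-week values. If 0.5 is the SD of change, this gives at least 83% power for a 0.4 difference at 25 per arm for r from 0.3 to 0.8.
2. Say that 0.4 is the assumed perhexiline-minus-placebo difference. If the pilot had a control group, use its between-group figure instead.
3. Restate power at the 50 recruited as 79% for a true difference of 0.4 with SD 0.5 (unadjusted t-test), and 55% for 0.3, both lower with dropout.

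The cost is wording and one recalculated figure. The baseline scan is already in the schedule, so no patients, visits or measurements are added. The stated power becomes slightly less favourable.
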